#### Data management of interview analysis for construction of a health promotion program

The analysis of the interviews will proceed in the 6 distinct main stages summarized here:Open codification of re-transcribed interviews in order to identify as many topics as possible from the initial corpus;Categorization of the codified elements; careful reading of the whole corpus so that each category is clearly defined, its properties revealed, the different forms and conditions of occurrence of the specified phenomena;Linking categories; writing more detailed memos and designing explanatory diagrams;Integration of the previous steps in order to identify the essence of the phenomenon;Modeling: the phenomenon, in addition to being described, defined, and explained, its dynamics will be examined and conceptualized. The structural and functional relationships of each of its constituents will then be highlighted;Theorization: a thorough and exhaustive construction of the “multi-dimension” and “multi-causality” of the phenomenon of associations between the needs, expectations, and representations of the different groups (health care users, carers, primary care and mental health professionals).

Interdisciplinary meetings with the steering committee will be organized throughout the analysis process, during which the framework will be adjusted according to the standard indications of the grounded theory if necessary. Triangulation of the data by researchers from different fields as well as experts by experience will guarantee a high level of both internal and external validity of the results once freed from the theoretical paradigms. The resulting data will serve as a basis for the construction of the health promotion program.

Qualitative data management will be done using NVIVO software.

### Feasibility study

#### Sample

This prospective, monocentric, non-comparative implementation trial will be carried out with the participation of service users of the newly developed health promotion program. It’s focus is the development of the implementation technique, determination of the endpoint of clinical efficacy, as well as the possible complications and risks. A sample of 30 participants [28] will be included from la Chartreuse Hospital in Dijon.

#### Eligibility and recruitment procedures

We anticipate that the health promotion program will target health care users first. As such, a random group of individuals with SMI and CVRF will be selected at la Chartreuse Hospital Center. The selected individuals will be matched for age, sex, and socio-professional category. Volunteers will be recruited after written information is provided by a health professional during routine outpatient or inpatient care. In the case of outpatient care, the health care team will call back undecided persons after 15 days.

In the event that parts of the health promotion program target carers or health professionals specifically, an adjusted recruitment method in line with literature standards will be implemented.

#### Data management

Changes in attitude among the intervention group participants will be documented. The results for qualitative covariables will be expressed in proportions. Quantitative variables will be expressed as means and standard deviations (SD) when they are normally distributed, or as medians in other cases. Comparison of the individual characteristics between a group of interest and the general population will be done with Student’s t-test, analysis of variance, Kruskal–Wallis non-parametric tests, and Pearson’s Chi Square or Fisher’s exact test. A value of p < 0.05 will be considered statistically significant. All analyses will be performed using SAS version 9.3 (SAS Institute INC). The electronic data will be stored on secure data servers provided by the Dijon University Hospital.

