#### Start of the study

The initial evaluation of participants will consist of:Collection of socio-demographic data: age, sex, socio-professional categories;An assessment of quality of life;An assessment using the Citizenship measure;An assessment of mental health recovery;An assessment of CVRF representations;An assessment of physical activity level;An evaluation of CVRF;A collection of medical history and treatments, including an assessment of lifestyle habits and substance use;Participation in the first stage of the health promotion program.

We anticipate that the program will take place over a period of 2 months and will be delivered by a pair of peer-support workers and people trained in health promotion. Sessions will be spaced approximately 15 days apart and will last approximately 1 h each. For reasons of feasibility due to concentration of participants, we estimate a need for 3 to 4 sessions, with an initial inductive session and a final evaluation session. Each session of the program will include no more than six participants. As a result, the program will be completed five times during the study period. A health care manager will be responsible for the technical coordination to ensure the practical organization of each group.

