#### 3-month visit

Participants will attend a 3-month evaluation session that will consist of measurements identical to those carried out in the inclusion visit.

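### The feasibility study's only stated tests compare participants with an unidentified general population, not with themselves before and after the programme

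*Protocol article*

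**What the plan says.** The Sample section for the feasibility study sets the design: "This prospective, monocentric, non-comparative implementation trial will be carried out with the participation of service users" of the new programme. It also sets the size: "A sample of 30 participants [28] will be included from la Chartreuse Hospital in Dijon".

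Under Interventions, Feasibility study, a set of assessments is taken at inclusion: quality of life, citizenship, recovery, representations of cardiovascular risk factors, physical activity and cardiovascular risk. It is then repeated: "Participants will attend a 3-month evaluation session that will consist of measurements identical to those carried out in the inclusion visit". The 6-month visit matches the 3-month one and is meant to show whether the programme has a lasting effect on participants' health. The section on construction of the programme also plans a questionnaire to capture change in representations before and after the programme.

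The Data management section for the feasibility study says that changes in attitude will be documented. It then states its one inferential comparison: "Comparison of the individual characteristics between a group of interest and the general population will be done with" the t-test, ANOVA, Kruskal–Wallis, chi-square and Fisher's exact test. The threshold follows: "A value of p < 0.05 will be considered statistically significant".

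**The concern.** The stated comparison does not fit the design. The design has one group, observed three times, and its own aim is change within those people. The comparison needs a second group or a reference value, and the article supplies neither.

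A team that followed the text would put its p-values on whether participants differ from some general population. It would have nothing specified beyond documentation for the change at 3 and 6 months. That change and its spread are among the main things this single-group study can pass on to the randomized trial it is meant to prepare.

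A second risk is practical. An analyst who finds no general-population data might apply the listed tests between visits instead, as if the visits were separate groups. That would discard the pairing.

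**Working it through.** **Step 1: is there a second group?** Participants are service users at one hospital. No general-population sample is recruited, and no norm or reference data set is named for the comparison. The eligibility section mentions matching on age, sex and socio-professional category but does not say to whom, so it does not supply a comparator.

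**Step 2: what do the named tests address?** Kruskal–Wallis, Pearson chi-square and Fisher's exact test assume independent observations. The t-test and ANOVA have paired and repeated-measures forms, but the sentence ties all five to a between-group comparison. No signed-rank, Friedman, McNemar or mixed-model analysis is mentioned.

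**Step 3: the sample size.** The 30 is not based on power; it rests on a cited reference. It agrees with the delivery plan: "Each session of the program will include no more than six participants", and "the program will be completed five times during the study period", so 5 × 6 = 30.

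**Step 4: size of the error if the tests were run between visits as independent groups.** This is conditional; the article does not state this use. Inputs are n = 30 and α = 0.05 from the article, taken as two-sided because sidedness is not stated. The between-visit correlation ρ is not in the article and is assumed to be 0.3 to 0.8. Outcomes are simulated as normal with equal SD at each visit.

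- SE of mean change, visits treated as independent: SD × √(2/n) = SD × √(2/30) = 0.258 SD.
- SE of mean change, paired: SD × √(2(1 − ρ)/n). At ρ = 0.5 this is SD × √(1/30) = 0.183 SD.
- Ratio: 1/√(1 − ρ).
- Change detectable with 80% power (normal approximation): (1.96 + 0.84) × SE.

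| Assumed ρ | 0.3 | 0.5 | 0.7 | 0.8 |
|---|---|---|---|---|
| Paired SE (SD units) | 0.216 | 0.183 | 0.141 | 0.115 |
| Ratio, independent to paired SE | 1.20 | 1.41 | 1.83 | 2.24 |
| Power for 0.5 SD change, independent t | 47% | 46% | 46% | 46% |
| Power for 0.5 SD change, paired t | 61% | 75% | 93% | 99% |
| Actual type I error, independent t | 2.1% | 0.7% | <0.1% | <0.1% |
| Detectable change, independent | 0.72 SD | 0.72 SD | 0.72 SD | 0.72 SD |
| Detectable change, paired | 0.61 SD | 0.51 SD | 0.40 SD | 0.32 SD |

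Power and type I error are simulated. The paired test held about 5% throughout. One-way ANOVA over the three visits behaves the same way: its type I error is 1.6% at ρ = 0.3 and 0.4% at ρ = 0.5, against about 5% for repeated-measures ANOVA.

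**The case against.** The strongest reply is that the table measures something the article does not plan. The Data management section never says the tests will be used between visits, and it plans no confidence intervals. This stands. The figures show what would follow from one possible misuse; they are not the consequence of the plan as written.

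A reader might infer that the stated analysis cannot be run at all. That goes too far. A one-sample comparison of participants' scores with a published norm needs no recruited second group. What is missing is the norm, and such a comparison would still say nothing about change at 3 and 6 months.

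It can also be said that the model for change belongs in the analysis plan and that an article condenses. That is fair for the choice of model. But this article does state a comparison, a list of tests, a threshold and the software, and that comparison is at odds with its own design. Shortening a within-person analysis would not turn it into a comparison with the general population.

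A reader might infer that the planning figures for the randomized trial would be wrong. The documents do not support this: an ill-chosen test leaves the mean and SD at each visit unchanged. Nor is the summary rule for quantitative variables, "expressed as means and standard deviations (SD) when they are normally distributed, or as medians in other cases", a ground for the point. Whether a measure of spread accompanies a median is reporting detail that an article may leave to the fuller document.

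**Conclusion.** The concern holds as a mismatch between the stated comparison and the design. That part rests on the text alone and needs no assumption. The tests are directed at a general population that is neither sampled nor identified, while the within-person change the study is built around is only to be documented.

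The numerical part is conditional on the tests being run across visits as independent groups, and its size depends on a correlation the article does not give. At the low end (0.3) the loss is modest; at 0.8 it is large. For positive correlation the direction is always conservative: real change would be missed, and false positives would not be created.

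This should be fixed, but it does not undermine the study. It is a feasibility trial with no stated primary hypothesis test and no power-based sample size, so the harm is lost information rather than a misleading claim of efficacy.

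**What to change.** Replace the general-population sentence in the feasibility study's Data management section with an analysis of within-participant change from inclusion to 3 months and to 6 months, reported with 95% confidence intervals. Suitable methods include the paired t-test or Wilcoxon signed-rank test, McNemar's or Bowker's test for categories such as the three-level Ricci-Gagnon profile, or a mixed model over the three visits. Report the SD of change as well, because it helps in planning the randomized trial.

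Delete the general-population comparison. If it is wanted, keep it only as a descriptive comparison of baseline scores with reference data that are named.

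The cost is wording only: the three visits already supply the data, and no further participants are needed.

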## Interventions

### Construction of a health promotion program

The inclusion visit will be conducted after confirmation of the inclusion criteria and submission of the information letter. The socio-demographic data (age, sex, level of education) and professional details (profession, specialty, mode and place of practice, years of experience) will be collected in order to stratify participants and provide the widest range of observations:Participation in the FG will be continuous over the first 6 months of the study, in a neutral, pleasant, and friendly place, in a relaxed atmosphere. The FG will be led by a pair of qualified health sociology researchers. One will moderate the FG and the second will take notes.Participation in the steering committee will take place on an ad hoc basis. The steering committee will be organized similar to the FGs.

Technical coordination will be managed by a referent in each center, mainly health care managers, to ensure the hands-on organization of the FGs.

### Feasibility study

The inclusion visit will take place during routine care after the inclusion criteria has been verified and a signed informed consent form has been obtained.

#### Start of the study

The initial evaluation of participants will consist of:Collection of socio-demographic data: age, sex, socio-professional categories;An assessment of quality of life;An assessment using the Citizenship measure;An assessment of mental health recovery;An assessment of CVRF representations;An assessment of physical activity level;An evaluation of CVRF;A collection of medical history and treatments, including an assessment of lifestyle habits and substance use;Participation in the first stage of the health promotion program.

We anticipate that the program will take place over a period of 2 months and will be delivered by a pair of peer-support workers and people trained in health promotion. Sessions will be spaced approximately 15 days apart and will last approximately 1 h each. For reasons of feasibility due to concentration of participants, we estimate a need for 3 to 4 sessions, with an initial inductive session and a final evaluation session. Each session of the program will include no more than six participants. As a result, the program will be completed five times during the study period. A health care manager will be responsible for the technical coordination to ensure the practical organization of each group.

#### 3-month visit

Participants will attend a 3-month evaluation session that will consist of measurements identical to those carried out in the inclusion visit.

#### End of the feasibility study

The study will end with a final 6-month evaluation that matches the 3-month evaluation. The aim will be to assess the lasting impact of the program on the health of the participants.

### Feasibility study outcomes

#### Quality of life: SF-12 scale

This standardized self-administered questionnaire of 12 items is often used in health economics studies as a variable in the calculation of a QALY (quality-adjusted life year) to determine the cost-effectiveness of health interventions [29].

#### Citizenship: citizenship measure

The standardized self-administered Citizenship measure questionnaire of 46 items covers 5 dimensions of citizenship: basic needs, involvement in community, self-determination, access to services, and respect by others [30].

#### Mental health recovery: recovery assessment scale

This standardized self-administered questionnaire of 24 items covers 5 dimensions of mental health recovery: personal confidences, willingness to ask for help, goal and success orientation, reliance on others, and no domination by symptoms [30].

#### CVRF representations

A questionnaire will be developed during the qualitative study according to scientific literature and themes emerging from the FGs and will be validated by the SC.

#### Physical activity level: ricci-gagnon score

The Ricci and Gagnon weekly physical activity level questionnaire [31] is a self-administered questionnaire measuring a score-based physical activity profile: inactive, active, or very active.

#### Cvrf: score

Assessment of CVRF will use the European SCORE system promoted by European and French national health authorities [32].

## Ethical considerations and dissemination

This research received ethical approval from the relevant French authorities concerned with ethics, individual privacy, and freedom: the Comité de Protection des Personnes (CPP IDF XI, April 11 2019), and the Commission Nationale de l’Informatique et des Libertés (CNIL).

The project outcomes will be disseminated through selected peer-reviewed journals, conference presentations, workshops, webinars and the EPSM Lille-Métropole, WHO Collaborative Centre network.

## Discussion

The life expectancy of persons with mental health problems is a global concern that affects high-income countries in particular [13]. In France, this gap is estimated between 12 and 16 lost years of life [11], and is estimated to affect 4 million people identified with a long-term illness due to a mental health problem [1]. This increase in mortality is also accompanied by an increase in physical morbidity, and more generally by a decrease in quality of life [2].

For too long, this question has been ignored or perceived solely from a biomedical perspective [14, 16], resulting in different conceptualizations and recommendations from medical experts and academic societies but no substantial impact on the health of users in daily practice [7]. It now seems apparent that this gap is not a consequence of ‘mental illness’, but a failure of our health systems to enable persons labelled ‘mentally ill’ to enjoy the best possible health [16]. These people are often discriminated against by primary health systems [3, 5, 6] and captured in the hermetic system of psychiatry. This reduces their access to prevention initiatives, but also exposes them to treatments, including drug treatments, that increase risks to their physical health, especially cardiovascular health [2, 3]. In addition, the psychiatric system is part of a social organization that marginalizes people with mental health problems, thereby reducing their access to opportunities for healthy behaviors and health promotion initiatives [15].

These findings, drawn from both clinical practice and scientific literature, resonate with recent initiatives for the recognition of the rights of persons with psycho-social disabilities. The implementation of the 2020–2030 SDG by the WHO is based on the recognition of the impact of psycho-social disability and prioritizes health promotion interventions over biomedical treatments [10, 14]. Moreover, in line with the Convention on the Rights of Persons with Disabilities, the UN has called for a transformation of health systems so that they can be rethought on the basis of human rights, and in particular the right to enjoy the highest attainable standard of physical and mental health [16].

Recently, the participation of the individuals most directly affected by illness has been highlighted, not only in their care, which should be based on the observance of free and informed consent, but also in the organization of health systems [22]. Recognizing the added value of knowledge by experience [23], our qualitative research project has been developed to highlight the behavior and perceptions of persons with SMI and carers to value the meaning these individuals give to CVRF and potential ways to improve them. Regular visits to a family doctor would impact CVRF and would demonstrate individual capacity to access health care, while more physical activity would positively impact the Ricci-Gagnon score. Both of these perspectives are positive steps towards prevention. Our design should allow for easy generation of ideas and hypotheses, leading to small but effective interventions in the existing health system. The participation of users and carers in the working group at the basis of this project has made it clear that part of the solution comes from increasing the literacy and empowerment of service users and their carers rather than from increasing the technicality of professionals, which was often the focus of previous interventions. A health promotion program aimed at empowering the persons directly concerned has therefore emerged as a valid approach.

This study will contribute to the inclusion of elements of experiential knowledge in the scientific literature, and it may serve as a starting point for other initiatives promoting the rights of persons with psycho-social disabilities or mental health problems. The next step will be to evaluate the effectiveness of this new tool through a randomized controlled trial.

## Data Availability

Data and materials will be shared upon request to [name] [name].

## Abbreviations

SMI: severe mental illness
CVRF: cardiovascular risk factors
WHO: World Health Organization
UN: United Nations
SDG: Sustainable Development Goals
SC: steering committee
FG: Focus Groups
CPP: Comité de Protection des Personnes
CNIL: Commission Nationale de l’Informatique et des Libertés
QALY: quality-adjusted life year
